**Background**

Type 1 diabetes mellitus is one of the most common chronic diseases in childhood (1,2,3). These individuals require lifelong insulin treatment and optimal metabolic control, which is important to prevent short- and long-term complications (4).

To achieve optimal metabolic control the day-to-day management is challenging for the child and their family and can have a major negative impact on their quality of life (5,6).

Optimizing metabolic control in children with T1DM has led to intensified research in improved insulin pump technology and augmenting the pump data with glucose sensor information (Sensor Augmented Pumps, SAPs) to improve outcomes. Continuous interstitial glucose monitoring is associated with decreased HbA1c levels increased time in glucose target and reduced time spent in hypoglycemia in individuals with type 1 diabetes using CSII, however better outcomes are associated with longer and continued use of the sensor (7).

One of the goals of optimized therapy is to achieve fewer glycemic excursions and to maintain glucose values in the normoglycemic range.

Alerts are programmed and used in SAPs in order to inform patients and their caregivers about hypo-and hyperglycemic events to allow them to respond quickly to such glycemic excursions.

Alerts, however, can be perceived as disturbing. A new CGM device, the Freestyle Libre **®** (FGM), addresses this by measuring continuously the interstitial glucose levels, but the results can only be obtained when the patient/caregiver actively scans the sensor: no alerts are given when glucose values increase or decrease, nor will information be available when the sensor is not scanned at least every 8 hours. No communication exists between the glucose measurement and the insulin pump. The advantage of the FGM is access to 24h glucose profiles without disturbing alerts.

Without any alerts, however, the symptoms of high or low glucose levels may be missed , and intervention delayed.

Although the ultimate treatment objective is to close the loop , and automate insulin administration based on an algorithm which regulates insulin administration based on the glucose values, without the human intervention, these systems with only minimal human intervention are not yet available for routine care (8).

The 640G Medtronic ® SAP includes a further step towards closing the loop by combining alerts with an automated insulin suspension, when over the next 30 minutes the predicted glucose level will reach a pre set too low value (SmartGuard feature) Duration of the suspension is flexible and insulin administration is restarted, when glucose values are increasing again and above the low glucose range. Alerts are given in these situations, either by vibration or sound, but if no action is taken, but the insulin administration will be temporarily suspended for a minimum of 30 minutes.

Fear of nocturnal hypoglycaemia is pervasive amongst parents of children with T1DM, and is associated with heightened vigilance by parents to control regularly their children’s blood sugar values or to check the sensor information during the night. This leads to chronic sleep interruption and to lack of sleep as well for the parents as for their children with diabetes. Recent data shows 99% of parents of children with T1DM are performing blood glucose checks on their child during the night to ensure their safety whilst sleeping [9] . This highly prevalent chronic sleep interruption affects both adults with T1D and parents/carers of children with T1D with negative effects on their daily functioning and well-being (9). Anxiety and fear of hypoglycemia may have an impact on diabetes management and may complicate meeting glucose targets in patients with type 1 diabetes (10,11)

The current study, an open label single centre randomised cross over study aims to evaluate the impact of a sensor augmented pump (SAP) with a predictive algorithm to suspend temporarily insulin administration (640G**®** with the Smart Guard feature) versus the use of the same pump for isnulin administration with ‘only’ continuous glucose measurements (not interacting with the pump, Freestyle Libre **®** ) on the time in glucose target , in hypo- and hyperglycemia. As exploratory endpoints, we include the effect on sleep and quality of life in children with type 1 diabetes and their caregivers.

**Objective**

To evaluate whether sensor augmented insulin pump (Medtronic Minimed 640G ®) with the SmartGuard feature, increases time in glucose target , and improves sleep quality and quantity and quality of life perception in patients with T1DM and their primary caregivers , when compared with pump treatment with only continuous monitoring with the Freestyle Libre ®.

**Primary outcome**

- Percentage of time in glucose target (3.9-8mmol/l) during the final 6 days, of a 5 week treatment arm , measured by the blinded CGM IPro2, during at week 5 and 13, based on a between arm comparison.

**Secondary outcome**

- Percent time spent below glucose target (<3.0mmol/l and < 2,5 mmol/l) measured by blinded CGM (I-Pro 2) during week 5 and week 13
- Percent time spent above glucose target (> 10 mmol/l) measured by blinded CGM (I-Pro2) during week 5 and week 13
- Total sleep and wake time, number of awakenings measured by wireless actigraph during baseline and week 5 and week 13, in the patients and at least one of their caregivers.
- Quality of sleep in patients and in at least one of their caregivers in the two treatment arms (Epworth sleepiness scale) during baseline and week 5 and week 13,
- Quality of life perception in children during baseline and week 5 and week 13,
- Quality of life perception in parent/caregiver during baseline and week 5 and week 13,
- Childrens Hypoglycemia Index in children during baseline and week 5 and week 13,
- Hypoglycemia fear survey in parent/caregiver during baseline and week 5 and week 13,
- Family responsibility scale during baseline and week 5 and week 13
- Impact of family responsibility scale on total sleep and wake time, number of awakenings
- Impact of time in glucose target on total sleep and wake time, number of awakenings
- Impact of age, gender and SES (socio economic status) on total sleep and wake time, number of awakenings
- Daily physical activity as measured by the wireless actigraph during baseline and week 5 and week 13
- Impact of daily physical activity as measured by the actigraph, on sleep.
- Comparison of sleep diary versus actigraph data.
- Severe hypoglycemic events (11).

**Sample size**

Based on our previous report as well as other pediatric historical data , the percent time spent in glucose target (3,9-8 mmol/l) in  the pediatric population is estimated to be 40- 50 % (not published personal data, 11). Assuming that an increase of 10-15 % in time in glucose target is considered as clinically meaningful, a significance level set at 5 % (two sided) and a power of 80%, a minimum number of patients of 31 per group  would be necessary. Taking into account the within subject standard deviation and a maximum 10 % of drop out , a sample size of 36 patients should be included in the study. .

**Inclusion criteria**

- Diagnosis of type 1 diabetes (e.g. at least 1 positive antibody)
- Duration of diabetes: ≥ 6 months
- Insulin pump treatment for at least 6 months
- Age: 6 to 14 years
- HbA1c ≤ 11%
- Written informed consent of the primary caregiver, assent of the patients

**Exclusion criteria**

- No parental consent
- Physical or psychological disease likely to interfere with an appropriate conduct of the study
- Current drug therapy knowing to interfere with glucose metabolism
- Chronic sleep medication in the primary caregiver or the patient

**Study design:**

Open label single centre randomized cross over study .

The details of the study are summarized in the Patient Parcours .

The treatment arms will last 5 weeks and will be followed by a wash out period of 3 weeks before the second treatment for another 5 weeks.

During the last week of the treatment arms, the I-Pro2 **®**, will be placed for 6 days for the blinded CGM evaluation.

Before starting and during the last week of each treatment period, the subjects will wear a wireless actigraph during 24 hours , 7 nights and days.

At the first visit (V0), the study is explained, detailed information on the devices and their use are provided. When consent/assent is given, the,patients will be randomised in equal numbers to one of the two treatment sequences (First 640G with SmartGuard and second with Freestyle Libre (FGM) or first 640G with FGM and second with SmartGuard)

At the visit (V1), patients and one parent will be invited to fill out the validated questionnaires. A baseline Hba1c value and demographic and clinical data will be obtained in the CRF.

Patients will start on the 640G pump without FGM and sensor. As all patients are pump treated, the use of the new device will be a simple transition. During this period, all patients will perform a minimum of 4 capillary glucose measurements daily. The patient and one caregiver will be provided with a wireless actigraph and will be asked to fill out the sleep diaries during the 7 days of actigraph wearing. When rendering the actigraphs, either the SmartGuard or the FGM will be initiated.

Setting of the Smart Guard are standardised based on the current experience.(12) The low limit will be set at 3.4 mmol/l , with an insulin suspension at ≤7.3 mmol/l if the predicted value within 30 minutes is 4,5 mmol/l. An alert before low will be on, which will inform parent/patient that insulin administration is suspended. The insulin administration will resume automatically after maximally 2 hours , or when the glucose values -after minimally 30 minutes without insulin administration- are above the lower limit and increasing or after 2 hours. The insulin administration can be resumed manually , overriding this SmartGuard feature.

At the next visit (V2) (after 4 weeks of treatment) the patient and families will be invited to complete the questionnaires. A Hba1c will be taken and CRF will be completed. The I-Pro 2 for blinded CGM will be placed for 6 days , and the patient will be instructed to introduce 2 glucose measurements /day for calibration. The wireless actigraphs will be provided. Patients and parents will be asked to fill out the sleep diaries during the following week.

This week will be followed by a wash out period of 3 weeks.

During the wash out period, the 640G pump will be maintained, but in combination with a minimum of 4 blood glucose measurements and no sensor nor FGM.

Sleep assessment with be conducted with actigraphs and sleep diaries 1 week before the start of the second treatment arm.

The second treatment period will be started at (V3) on either the FGM or the SmartGuard feature.

After 4 weeks, at V4, the CRF and the questionnaires will be completed , the I-Pro 2 for blinded CGM, will be placed. Wireless actigraphs are provided and patients and parents will be asked to fill out the sleep diaries.

Detailed description of the study visits is provided in the ‘parcours patient.

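### Randomisation at consent (V0) comes before the baseline questionnaires and sleep week in an open-label trial; moving it to device start is a cheap, minor improvement

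*Protocol*

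**What the plan says.** The Study design section of the Protocol describes an "Open label single centre randomized cross over study". It gives the opening steps in this order:

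- V0: "At the first visit (V0), the study is explained, detailed information on the devices and their use are provided". Randomisation belongs to the same step: once consent and assent are given, "patients will be randomised in equal numbers to one of the two treatment sequences".
- V1: "At the visit (V1), patients and one parent will be invited to fill out the validated questionnaires", and "A baseline Hba1c value and demographic and clinical data will be obtained in the CRF".
- Baseline week: patients use the 640G with neither sensor nor FGM. The patient and one caregiver wear actigraphs and "will be asked to fill out the sleep diaries during the 7 days of actigraph wearing".
- Device start: "When rendering the actigraphs, either the SmartGuard or the FGM will be initiated".

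The Statistical analysis section lists baseline beside weeks 5 and 13 as a time point for sleep, quality of life, sleepiness and fear of hypoglycaemia. The primary outcome, time in glucose target by blinded CGM, is compared at weeks 5 and 13 with treatment, sequence and period in the model and no baseline term.

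The Sample size section asks for 31 patients, allows at most 10% drop-out and sets 36 to be included.

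**The concern.** Between V0 and the return of the actigraphs every family does the same things: the same pump, capillary measurements, questionnaires, actigraph and diary. No step needs to know the sequence, so allocating at V0 gains nothing, and it has two drawbacks.

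First, much of the baseline is self-reported (sleepiness, fear of hypoglycaemia, quality of life, sleep diary). A family that already knows whether SmartGuard or Libre comes first may answer differently because of it. The baseline would then no longer be a clean pre-allocation measurement, and baseline differences between the sequences could not be put down to chance alone.

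Second, a family that withdraws during the run-in has already been randomised. It contributes no outcome on either device, and the equal split between sequences may be lost. The Protocol states no replacement rule.

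**Working it through.** **Order of events.** Consent and randomisation (V0), then questionnaires and HbA1c (V1), then 7 days of actigraphy and diary, then first device. All of this comes from the Study design section, and nothing elsewhere in the Protocol gives a different order.

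**Where a baseline shift would go.** Let B be a patient's single baseline value, and Y1 and Y2 the values at the end of the two periods. Suppose knowledge of the order moves B by a in the SmartGuard-first sequence and by b in the Libre-first sequence.

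- Device against device, within patient: (Y1 − B) − (Y2 − B) = Y1 − Y2. The shift drops out.
- Baseline, sequence against sequence: off by a − b.
- Each device against baseline, with equal sequences: the baseline mean is off by (a + b)/2, so both device-versus-baseline differences are off by that amount.
- Primary outcome: B does not appear.

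The cancellation assumes one common baseline. The Protocol also has a sleep assessment before the second period, but it does not say that this serves as a separate period baseline.

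**Sample size, the plan's own figure.** The 31 is read here as the total number of completers, because 36 is the total to be included.

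- 31 / (1 − 0.10) = 34.4, rounded up to 35. The next even number, for two equal sequences, is 36. The stated 36 is reproduced to within one patient.
- Spare places: 36 − 31 = 5, and 5/36 = 13.9%. The stated 10% of 36 is 3.6, so 36 holds a little more than the 10% allowance.

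**If the 10% covers the run-in:** 36 × 0.90 = 32.4 expected completers, above 31. No shortfall.

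**If the 10% applies only after device start (assumption)**, with a further run-in loss r. The Protocol gives no value for r, so a range is shown.

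| r | Expected completers, 36 × (1 − r) × 0.9 | Randomised at V0 to keep 31, 31 / (0.9 × (1 − r)) |
|---|---|---|
| 0% | 32.4 | 35 |
| 3% | 31.4 | 36 |
| 5% | 30.8 | 37 |
| 10% | 29.2 | 39 |

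**Power on the same assumption.** The Protocol gives no value for the SD. The SD of the within-patient difference that yields 80% power with 31 completers (two-sided 5%, t-test with n − 2 degrees of freedom) is 19.2 points for a 10-point effect, or 28.8 for a 15-point effect. The power figures are the same in both cases. Completers are (36 − k) × 0.9, rounded down, where k is the number of families lost in the run-in.

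| k | Completers | Power |
|---|---|---|
| 0 | 32 | 81.3% |
| 1 | 31 | 80.0% |
| 2 | 30 | 78.6% |
| 3 | 29 | 77.1% |
| 5 | 27 | 73.9% |

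**The case against.** The strongest reply is that the trial's main comparison is untouched. The primary outcome is measured by blinded CGM and uses no baseline value. Every patient receives both systems, and a shift in a common baseline cancels in the device contrast. The Statistical analysis section specifies no change-from-baseline analysis; it only lists baseline as a time point. Part of the baseline (actigraphy) is recorded by an instrument. All of this stands and keeps the severity low.

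Three stronger readings are tempting, and the Protocol supports none of them.

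- *Families know the order when they answer.* The Protocol says when patients are randomised, not when they are told. Open label does not settle the moment of disclosure, and visit detail is deferred to a patient schedule that is not in the reviewed text. Knowledge at baseline is possible but not shown.
- *One sequence waits 8 weeks for a device.* The second system does start about 8 weeks after the first (5 weeks of treatment plus 3 of wash-out). But every family begins a sensor system straight after the baseline week, so the sequences differ only in which one comes first.
- *Run-in losses leave the trial too small.* Nothing restricts the 10% to losses after device start, no run-in loss rate is given, and even one run-in loss on top of a full 10% leaves 31 completers.

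It is also fair to say that the remedy is partial. At the sleep assessment before the second period, every family knows what comes next, whenever randomisation took place.

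What remains is that the Protocol fixes allocation earlier than any step requires, and nothing in it protects the self-reported baseline from knowledge of the order.

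**Conclusion.** The point holds as a cheap improvement of minor severity. The order of events is plain in the text. The consequences are confined to three places:

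- self-reported baseline values and comparisons of either device with baseline, if the order is disclosed before V1 or during the sleep week (not stated);
- balance between the sequences, if families leave before a device starts;
- the number of completers, modestly, and only if the 10% drop-out does not already cover the run-in (an assumption). On that reading, expected completers fall just below 31 at a 5% run-in loss, and three such losses put power at about 77%, with the SD back-solved from the plan's own 31.

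The documents do not support a claim that the SmartGuard-versus-Libre comparison is biased, or that 36 is inadequate.

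**What to change.** In the Study design section, move randomisation from V0 to the return of the baseline actigraphs, once the V1 data and the sleep week are complete and immediately before SmartGuard or Libre is started. State that the 36 counts patients randomised at that point.

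If randomisation has to stay at V0, keep the allocation closed to families and site staff until the actigraphs are returned, and say whether the 10% covers losses before device start and whether such patients are replaced. This protects the baseline answers, but families who leave early would still be among those randomised.

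The change is about one sentence of protocol text. Both device kits must be ready at the start visit, and a few more families may have to be consented to reach 36 randomised. The other visits, the treatment periods and the analysis model stay as they are.

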**Study material:**

- Insulin pump: Minimed 640G, Medtronic
- Glucose sensors: Freestyle libre ®, Abbott and Enlite® sensor, Medtronic Glucometer for capillary measurements: Contour Next®, Ascensia
- iPro®2 Professional CGM, Medtronic
- Wireless sleep monitor ( LIH), Actigraph ®
- Questionnaire Children (13)
- Questionnaire Parents ( Parents/Caregiver) (14)
- Diaries
- Case Record Forms
- Time schedule
- Patient information and informed assent
- Parent Information and informed consent

Data management TBD ( LIH_DECCP)

Ennov Clinical will be used for the data management throughout the study. Ennov Clinical is a global DM software allowing the design of data entry mask, data entry, cleaning of the database through consistency edit checks, medical coding if needed with WHO DD and MEDDRA and quality control of the database before freezing.

The data entry mask will reproduce the CRF to avoid data entry errors at maximum.

Data analysis of the Actigraph will bedone in collaboration with LIH –

[name], dr [name].

**Statistical analysis (15)**

Time in glucose target will be evaluated by the blinded CGM at the end of both treatment arms.

Percent time :

- In Glucose target (3.9-8 mmol/l) during the final 6 days, of a 5 week treatment arm measured by blinded CGM during week 5 and week 13
- Below glucose target (< 3.0 mmol/l and < 2,5 mmol/l) during the final 6 days, of a 5 week treatment arm measured by blinded CGM during week 5 and week 13
- Above glucose target ( > 10 mmol/l) during the final 6 days, of a 5 week treatment arm measured by blinded CGM during week 5 and week 13

will be compared between arms by using a linear model with treatment, sequence of treatments, period as fixed effect.

Total sleep and wake time, number of awakenings at baseline, week 5 and week 13, in patients and at least one of their caregivers will be analysed using a linear model with treatment given and period of treatment as fixed effects factors and patient as a random effect.. Impact of family responsibility scale will be tested in the model, as well as time in target, age, gender and SES (socio economic status), daily physical activity.

Quality of life perception and Quality of sleep in patients and in at least one of their caregivers in the two treatment arms (Epworth sleepiness scale) at baseline, week 5 and week 13, will be analysed by using a linear model or a model for categorical outcome depending on the final type of the studied variable.

Hypoglycemia Index in children and Hypoglycemia fear survey in parent/caregiver

at baselines, week 5 and week 13, will also be analysed with the model specific to cross-over trials.

A comparison of sleep diary data versus Actigraph data will be carried out.

Severe hypoglycemia ( defined by ISPAD . (11) will be analyzed through a table of frequencies.

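### The model stated for the primary outcome names no patient effect; fitted as written to cross-over data, it overstates the standard error of the treatment difference

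*Protocol*

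**What the plan says.** Under Study design the protocol describes an "Open label single centre randomized cross over study", with children "randomised in equal numbers to one of the two treatment sequences". The primary outcome is measured by blinded CGM at the end of each treatment period (weeks 5 and 13), so a child who completes contributes two values.

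Under Statistical analysis, the percentages of time in, below and above glucose target "will be compared between arms by using a linear model with treatment, sequence of treatments, period as fixed effect". Those three terms are all that is listed.

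The next paragraph of the same section handles total sleep time, wake time and awakenings with a "linear model with treatment given and period of treatment as fixed effects factors and patient as a random effect". The hypoglycaemia questionnaires "will also be analysed with the model specific to cross-over trials".

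The Sample size section arrives at 31 patients per group for 80% power at a two-sided 5% level, then at 36 patients in the study, "Taking into account the within subject standard deviation and a maximum 10 % of drop out". It gives no value for that standard deviation.

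**The concern.** In a cross-over the treatment comparison is made within the child, and its error is the within-child variance. That requires a patient term, random or fixed, or an equivalent analysis of within-child differences. A linear model with only treatment, sequence and period leaves the differences between children in the residual. Treatment is then tested against between-child plus within-child variance.

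The protocol is not silent here: it lists the terms of the primary model, and the list differs from the one it gives for sleep a few lines later. An analyst who follows the sentence literally would fit ordinary least squares to two rows per child. At stake are the confidence interval and p-value of the primary outcome and of the other glucose outcomes. With complete, balanced pairs the point estimate is unaffected.

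**Working it through.** **Inputs from the protocol.** Two sequences, two periods, equal allocation; two-sided 5%; 80% power; an effect of 10-15%, read here as percentage points; 31 per group; 10% dropout; 36 patients. **Assumed, because not given:** the SD, and the within-patient correlation rho, shown at 0.3, 0.5 and 0.7.

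**The plan's own figure.** The 31 cannot be reproduced forwards without an SD. Solving n = 2 × (SD × (1.960 + 0.842) / delta)² backwards for n = 31 gives:
- delta 10: SD = 10 × sqrt(31/2) / 2.802 = 14.05
- delta 15: SD = 15 × sqrt(31/2) / 2.802 = 21.08

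The same formula gives patients per arm when the SD is the total SD (parallel groups), and total patients when it is the within-subject SD (cross-over). The number 31 therefore does not show which SD was used. The dropout step is consistent: 31/0.9 = 34.4, so 35, and 36 is the next even number. Completers: 36 × 0.9 = 32.4, so 32.

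**Standard error.** Let sb² and sw² be the between- and within-child variances, rho = sb²/(sb² + sw²), with n complete children split equally.
- True variance of the treatment estimate: 2sw²/n.
- The residual of the model as written has 2n - 4 degrees of freedom: n - 2 between children with expectation 2sb² + sw², and n - 2 within children with expectation sw². The average is sb² + sw², so the reported variance is 2(sb² + sw²)/n.
- Ratio of standard errors: sqrt((sb² + sw²)/sw²) = 1/sqrt(1 - rho).

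At rho 0.3, 0.5 and 0.7 this is 1/sqrt(0.7) = 1.20, 1.41 and 1.83. It does not depend on the SD.

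**Type I error and power**, by simulation of the cross-over with 16 completers per sequence and at least 20,000 trials per setting.

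*Reading A: the sizing SD is within-subject.* The SD is set at 13.79 (paired-difference SD 19.5), so that the analysis with a patient term has 80% power for 10 points.

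| rho | True SE | SE as written | Type I error as written | Power as written | Power with patient term |
|---|---|---|---|---|---|
| 0.3 | 3.45 | 4.12 | about 2% | about 70% | 80% |
| 0.5 | 3.45 | 4.88 | 0.7% | 53% | 80% |
| 0.7 | 3.45 | 6.29 | 0.1% | 25% | 80% |

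The true SE is 13.79 × sqrt(2/32) = 3.45. Using 14.05 instead lowers the power as written by one to two points.

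*Reading B: 14.05 is the total SD.* The SE as written is 14.05 × sqrt(2/32) = 3.51 at every rho.

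| rho | True SE | Power as written | Power with patient term |
|---|---|---|---|
| 0.3 | 2.94 | 84% | 91% |
| 0.5 | 2.48 | 88% | 97% |
| 0.7 | 1.92 | 93% | >99% |

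**The other end of the effect range.** With the SD of reading A, a 15-point effect gives the model as written 97%, 93% and 75% power. If the trial was instead sized on 15 points, the SD scales with the effect (21.08) and the reading A powers apply at 15 points, less the same one to two points.

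**The case against.** The strongest reply is that a cross-over model was intended all along. The sentence lists fixed effects, and a random patient effect would not belong in such a list. A sequence term is usual beside patient-within-sequence. The word "also" in the questionnaire sentence ("will also be analysed with the model specific to cross-over trials") suggests that the earlier models were meant as cross-over models, nothing excludes a patient effect, and an SAP may supply one. This is a fair account of likely intent, and it means that an unpaired analysis is the literal reading and not a certainty. It does not supply the term. The questionnaire sentence concerns other outcomes, the section contains two different models to which it could refer, and the authors wrote the patient effect out for sleep but not for the primary outcome.

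Four stronger readings are tempting and are not supported:
- *The stated 80% power is not delivered.* This needs reading A. The reference to a within-subject SD favours it, but per-group wording is parallel-group language, and under reading B 80% is met. With no SD, no correlation and an effect given as a range, the protocol does not decide the matter.
- *A false-positive risk for the primary outcome.* The error runs the other way: type I error is below 5%.
- *False carry-over signals.* The sequence term would be tested against too small an error, but the protocol uses it only as an adjustment and attaches no decision to it.
- *The same fault in the Epworth and quality-of-life analyses.* Those "will be analysed by using a linear model or a model for categorical outcome depending on the final type of the studied variable"; that leaves the model open, which is ordinary detail for an SAP.

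**Conclusion.** The point holds for the primary outcome and the other glucose outcomes. The stated model omits the patient effect that the sleep model carries. Fitted literally, with positive within-patient correlation, it overstates the treatment standard error by 1/sqrt(1-rho), or 20% to 83% over rho 0.3 to 0.7. The consequence is an interval that is too wide, a conservative test and the loss of the precision that the cross-over was chosen to give. The inflation factor rests on complete, balanced pairs, equal variances in the two periods and a positive correlation, but on no assumed SD. The effect on the 80% power is conditional on which SD lies behind the 31 and cannot be computed from the protocol. The defect deserves correction before analysis because it affects the primary interval and p-value, and because a patient term added after the data are seen would look post hoc.

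**What to change.** In Statistical analysis, state that time in, below and above target will be compared with a linear mixed model with treatment, period and sequence as fixed effects and patient (nested in sequence) as a random effect. With complete pairs this gives the same treatment test as a t-test on within-child period differences. If an SAP already contains the term, bring the protocol sentence into line with it.

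It would also help to state in Sample size the SD used, whether it is within-subject or total, and the single effect size behind the 31, so that the 80% can be checked against the model.

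The cost is one clause in the protocol or SAP, with no extra patients, visits or data.

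### In the sleep model, the slopes for time in target, physical activity and family responsibility each blend a within-child with a between-family association, and should be split and reported as associations

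*Protocol*

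**What the plan says.** The Statistical analysis section of the protocol analyses total sleep time, wake time and number of awakenings, in patients and at least one caregiver, with a "linear model with treatment given and period of treatment as fixed effects factors and patient as a random effect". It then says: "Impact of family responsibility scale will be tested in the model, as well as time in target", and the same sentence adds age, gender, SES and daily physical activity.

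The Secondary outcome section lists these as outcomes in their own right: "Impact of time in glucose target on total sleep and wake time, number of awakenings"; "Impact of daily physical activity as measured by the actigraph, on sleep"; "Impact of family responsibility scale on total sleep and wake time, number of awakenings". A further item uses the same word, impact, for age, gender and SES.

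Three of the covariates are measured more than once:
- Time in target, at the end of each arm only: "Time in glucose target will be evaluated by the blinded CGM at the end of both treatment arms".
- Responsibility, at three listed times: "Family responsibility scale during baseline and week 5 and week 13".
- Activity, likewise: "Daily physical activity as measured by the wireless actigraph during baseline and week 5 and week 13".

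Under Study design, only the order of the two treatments is randomised.

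**The concern.** A covariate that varies over time carries two kinds of information. One is how sleep differs between weeks in which the same child has a higher or lower value. The other is how sleep differs between families whose average values differ. A model with a random patient intercept and one slope per covariate combines the two. The combined slope estimates the within-child association only if the child-level part of sleep is unrelated to the covariate.

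Nothing in the design secures that. The Background section itself describes parental fear and vigilance as disturbing sleep, and says that fear of hypoglycaemia may complicate meeting glucose targets. That is a plausible family-level common cause.

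At stake is the reading of three named secondary outcomes. A significant slope could be reported as an impact on sleep when it reflects only that some families differ from others. A within-child association could also be diluted or reversed by an opposite association between families.

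**Working it through.** **Inputs.** The protocol gives no figure for this analysis. From it come the model, the 36 patients (Sample size section), two occasions for time in target and three for activity and responsibility. Three quantities are assumed because the documents give none: the intraclass correlation (ICC) of the covariate, the ICC of sleep, and the correlation r between their child-level parts. All variables have SD 1, and the true within-child slope is 0.

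**What the single slope estimates.** With T occasions per child:
- between-family slope: b_B = r × √(ICC_x × ICC_y) / (ICC_x + (1 − ICC_x)/T)
- covariate information per child: within S_W = (T − 1)(1 − ICC_x); between S_B = T × ICC_x + (1 − ICC_x)
- discount on between-family information: φ = σ²_e / (σ²_e + T × σ²_u), where σ²_e and σ²_u are the residual and patient variances of sleep
- single slope = w × b_B + (1 − w) × b_W, with w = φ S_B / (S_W + φ S_B)

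Example with T = 2, ICC_x = 0.7, ICC_y = 0.5, r = 0.5:
- b_B = 0.5 × √0.35 / 0.85 = 0.348
- S_W = 0.3 and S_B = 1.7
- φ = 0.5 / (0.5 + 2 × 0.5) = 0.333
- w = 0.567 / 0.867 = 0.654
- single slope = 0.654 × 0.348 = 0.23 SD per SD, although b_W = 0

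The simulated mean slope for this case is 0.243. The small gap arises because φ rises slightly once the slope is fitted.

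**How often it is significant.** Simulated cross-over with 36 children, two occasions, REML random-intercept fit with treatment, period and one covariate, 2,000 runs per row, 5% two-sided:

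| ICC covariate | ICC sleep | r | Single slope | Within-child slope |
|---|---|---|---|---|
| 0.5 | 0.5 | 0.3 | 15% | 5% |
| 0.5 | 0.5 | 0.5 | 35% | 5% |
| 0.5 | 0.7 | 0.3 | 14% | 5% |
| 0.5 | 0.7 | 0.5 | 30% | 6% |
| 0.7 | 0.5 | 0.3 | 20% | 5% |
| 0.7 | 0.5 | 0.5 | 50% | 5% |
| 0.7 | 0.7 | 0.3 | 21% | 5% |
| 0.7 | 0.7 | 0.5 | 52% | 5% |

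- **Three occasions** (activity, responsibility): 13% to 49%, with the low end at 11% to 12% in repeat runs. The mean slope is 0.06 to 0.20, against 0.09 to 0.24 with two occasions.
- **r = 0:** the single slope rejects in 5% to 7%, so there is no material inflation.
- **31 completers** (ICCs 0.7 and 0.5): 21% at r = 0.3 and 47% at r = 0.5.
- **With a measured child-level factor in the model,** standing in for age, gender and SES: if it carries half of the shared child-level part, rejection is 9% and 21% at r = 0.3 and 0.5 (ICCs 0.7 and 0.5), and 7% to 18% at ICCs 0.5/0.5 and 0.7/0.7. If it carries all of it, about 5%. The share is an assumption.

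**Price of the split.** The standard error of the within-child slope relative to the single slope is about √((S_W + φ S_B)/S_W). In the example this is √(0.867/0.3) = 1.70. Over the ICCs in the table, simulation gives about 1.2 to 1.8. With a covariate ICC of 0.9 (an almost constant family scale) it is 2.2 to 3.0 with two occasions and 1.7 to 2.3 with three.

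**The case against.** The strongest reply has four parts.

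**The protocol does not say that each covariate is entered undivided.** Testing an impact in the model is compatible with a mean-plus-deviation coding, and an analysis plan that is not shown could specify it. This stands in part: the split is not excluded. But the plain reading of the sentence is one term per covariate, and nothing in it points to a split.

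**Impact need not mean a within-child effect.** The Secondary outcome section uses the same word for age and gender, which cannot be studied as changes within a child here. For family responsibility, a comparison between families is a natural question. This stands. A reader might infer from the table that up to half of such findings would be false. The documents do not support that, because a slope that picks up a real between-family association is wrong only if it is read as within-child. What remains is that one slope answers neither question cleanly.

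**Age, gender and SES are named in the same sentence.** If entered jointly, they would absorb part of the shared variation. This stands too, and the unadjusted rates must be labelled as such. Traits that these three do not capture remain.

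**The within-child slope is not randomised either.** Poor sleep may affect glucose control, and night-time checks may affect both. This stands fully. A reader might infer that the deviation slope is the true impact, but the design gives no basis for that. The split removes stable family differences, not confounding that varies from week to week.

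**Conclusion.** The point holds as a low-priority improvement to secondary analyses. As written, each of the three repeatedly measured covariates has one slope that averages a within-child and a between-family association, and nothing in the design makes the two equal. Under the assumed ICCs and correlations, that slope is significant without any within-child association in roughly 13% to 52% of trials before adjustment for age, gender and SES. The rate is lower after adjustment, by an amount that the documents do not allow one to fix, and about 5% if child-level covariate and sleep are uncorrelated. Every rate rests on correlations that the protocol does not give, so the result is a possibility with a range, not a predicted error rate.

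A reader might also infer that the treatment comparison is compromised. It is not: the argument concerns the covariate slopes only. The primary outcome and the sample size are untouched, and the Background section describes the sleep and quality-of-life endpoints as exploratory.

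**What to change.** In the sleep paragraph of the Statistical analysis section, replace each of time in target, daily physical activity and family responsibility by two terms: the child's own mean over the assessed weeks, and each week's deviation from that mean. Time in target has two occasions, weeks 5 and 13; activity and responsibility have three, with baseline. Keep treatment, period, random patient, age, gender and SES in the model.

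Report both slopes: the deviation as the within-child association and the mean as the between-family association. Describe both as associations, since neither is randomised, and align the three items under Secondary outcome. Age, gender and SES stay as single terms, also described as associations.

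The cost is a few sentences and two derived terms per covariate, with no new data or visits. The downside is precision: the within-child standard error is about 1.2 to 1.8 times that of the single slope, and about 2 to 3 times for a nearly constant covariate. The deviation slope for family responsibility may therefore be too imprecise to say much, and the text should acknowledge this in advance.
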